**Methods/design:**

We will conduct a multi-centre, open-label, randomized, non-inferiority trial to compare short-course therapy (SCT) with conventional long-course therapy (LCT) in treating patients with acute cholangitis. SCT consists of 5-day intravenous antimicrobial therapy if the patients had clinical improvement, while at least 7 days of intravenous antibiotics will be provided to the LCT group. The primary outcome is clinical cure at 30 days after onset. Patients will be randomly assigned in an open-label fashion. A total sample size of 150 was estimated to provide a power of 80% with a one-sided α level of 2.5% and a non-inferiority margin of 10%.

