### Assessment and follow-up

Clinical assessment is performed at baseline and daily throughout the study treatment, at the end of therapy (EOT), and at discharge from the hospital or 30 days after onset (end of study, EOS).

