### Outcome measures

The primary outcome is clinical cure at 30 days after onset (EOS). Clinical cure is defined as disappearance of all clinical symptoms which were present upon diagnosis.

The secondary outcomes are clinical improvement after 30 days, mortality at day 30 after the diagnosis, or in-hospital mortality, occurrence of adverse effects, and recurrence or complications of acute cholangitis. Clinical improvement is defined as decrease but not disappearance of clinical symptoms which were present upon diagnosis.

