### Statistical analysis

We will analyse data using both ITT and per-protocol analyses. The per-protocol analysis population will consist of all randomized patients who are not lost to follow-up and have no major protocol deviations. We will attest the non-inferiority of the primary outcome on the basis of the normal theory test for binomial proportions. We will conduct the primary analysis without adjustment of potential confounders.

Secondary outcomes will also be analysed under a non-inferiority assumption, as appropriate. Pre-defined subgroup analyses for the primary and secondary outcomes include (1) presence or absence of septic shock at diagnosis; (2) presence or absence of bacteraemia; (3) initial antibiotics covering or not covering causative organisms; (4) Gram-positive organisms causing cholangitis; and (5) quick Sequential Organ Failure Assessment (qSOFA) score.

Clinical outcomes are confirmed by the investigators either by calling the patients by telephone or seeing them at an outpatient clinic visit, or by checking the clinical chart if the patient is still hospitalized.

All *P* values are one-sided, and *P* < 0.025 is considered statistically significant. All statistical analyses will be performed using STATA version 15.0 (StataCorp, College Station, TX, USA), and R version 3.5.1 (the R Foundation for Statistical Computing, Vienna, Austria).

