## Discussion

The current trial will examine whether SCT for acute cholangitis with appropriate biliary duct drainage is not inferior to conventional LCT. A retrospective cohort study with propensity score analysis suggested that the efficacy of SCT as well as occurrence of complications are similar to those of LCT [6]. If non-inferiority was achieved, SCT has several advantages over LCT in terms of length of hospital stay, potential adverse effects from antimicrobial therapy, cost, and emergence of antimicrobial resistance [7–10].

The current proposed trial has some inherent limitations. First, for practical reasons, we were not able to design the study to be double-blinded. Both patients and investigators will know to which group the patients belong. However, we consider that the outcomes we set are obvious and would not be likely to be impaired significantly by the trial being an open-label design, as demonstrated in a previous similar study [14]. Second, since clinical outcomes will be judged by our investigators, there is an inherent issue of potential subjectivity on outcome judgement. On the other hand, based on the previous study with a very high cure rate, we believe this is a relatively small problem unlike treatments of diseases with a lower success rate. In addition, it is not practical to employ independent investigators in multi-centre settings. Third, because this study is conducted solely in Japan, although it is a multi-centre trial, the results of the study might not be applicable in different settings outside the country. The results of the proposed study are not applicable to those patients with acute cholangitis when bile duct obstruction remains.

To the best of our knowledge, this will be the first trial to answer the clinical question of whether shortening of antimicrobial therapy for the treatment of acute cholangitis is possible without impairing treatment safety and efficacy. We hope that the trial aids in establishing a novel therapy to optimize the duration of antibiotic therapy for this rather common disease.

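### End of study is given as discharge or day 30 in one section and as day 30 in another, leaving room to read the primary outcome at discharge

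*Protocol article*

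**What the plan says.** Four places in the protocol article bear on when the primary outcome is read.

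- **Assessment and follow-up:** after the daily and end-of-therapy assessments, the last one is "at discharge from the hospital or 30 days after onset (end of study, EOS"). No rule says which alternative applies, or whether the earlier or the later governs.
- **Outcome measures:** "The primary outcome is clinical cure at 30 days after onset (EOS"). The same label is used, with day 30 alone. Cure is a symptom-based state: "Clinical cure is defined as disappearance of all clinical symptoms which were present upon diagnosis". Recurrence is listed separately among the secondary outcomes, without a time window.
- **Abstract, Methods/design:** "The primary outcome is clinical cure at 30 days after onset".
- **Statistical analysis:** "Clinical outcomes are confirmed by the investigators either by calling the patients by telephone or seeing them at an outpatient clinic visit". Inpatients have a route of their own, a check of their records. No day is given for any of these contacts.

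The Discussion adds that, if non-inferiority is shown, "SCT has several advantages over LCT in terms of length of hospital stay". Under Trial interventions, the minimum intravenous course is 5 days in SCT and 7 days in LCT.

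**The concern.** The primary outcome is attached to a label that has two meanings. A site working from the follow-up section could record the final assessment at discharge and regard the patient as complete.

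Patients generally leave hospital when they are well, so a symptom-based cure is likely to be met by nearly everyone at that moment. The plausible harm of stopping antibiotics earlier is relapse afterwards, and a discharge reading removes much of the window in which it would show. In a non-inferiority trial, failures that go unseen pull the observed difference towards zero and so towards a positive conclusion.

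Discharge is also a post-randomisation event that the treatment is expected to influence, so the assessment day could differ by arm. The trial is open-label and its own investigators judge the outcome, so a choice between two assessment dates adds discretion at an awkward place.

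**Working it through.** **1. The plan's own figure.** Inputs from the Sample size section: cure 95% in both arms, margin 10 points, one-sided α 2.5%, power 80%. With unpooled variance,

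n = (1.960 + 0.842)² × (2 × 0.95 × 0.05) / 0.10² = 74.6, so 75 per arm.

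This matches the stated 75 per group; normal-theory power at 75 is 80.2%. The point disputes no stated number, and reading everyone at day 30 leaves the sample size as it is.

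**2. The passages side by side.**

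| Section | Time given | Label |
|---|---|---|
| Abstract | day 30 after onset | none |
| Assessment and follow-up | discharge, or day 30 after onset | EOS |
| Outcome measures | day 30 after onset | EOS |
| Statistical analysis | telephone, clinic or chart; no day | none |

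The second and third rows disagree. The fourth favours day 30, since telephone and clinic contact presuppose that the patient has gone home, but it does not fix the day.

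**3. Illustration of the size.** The documents give neither discharge days nor relapse rates, so every input here is an assumption except the 75 per arm, the margin and the minimum courses of 5 and 7 days.

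- Persistent failure: 3% in both arms.
- Relapse by day 30: 12% SCT, 2% LCT. True failure is then 15% v 5%, exactly at the margin.
- Relapses are spread evenly from end of therapy (day 5 or 7) to day 30.
- Discharge on day 7 (SCT) and day 10 (LCT).

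Share of relapses seen by discharge: SCT (7 − 5)/25 = 0.08; LCT (10 − 7)/23 = 0.13.

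If everyone is read at discharge, observed failure is

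- SCT: 0.03 + 0.12 × 0.08 = 0.0396
- LCT: 0.03 + 0.02 × 0.13 = 0.0326

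The 10-point difference appears as 0.7 points.

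If a share s of patients in each arm is read at discharge, observed failure is 0.03 + r × [s × c + (1 − s)], where r is the arm's relapse rate and c its share seen. For s = 0.25: SCT 0.03 + 0.12 × 0.77 = 0.1224; LCT 0.03 + 0.02 × 0.783 = 0.0457.

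The probability of declaring non-inferiority is found by exact enumeration of both binomials at 75 per arm. Non-inferiority is declared when the upper 97.5% limit (unpooled standard error) for the difference in failure is below 10 points.

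| Share read at discharge (days 7/10) | P(declare non-inferiority) |
|---|---|
| 0% | 3.7% |
| 10% | 5.6% |
| 25% | 10.4% |
| 50% | 25.9% |
| 100% | 85.9% |

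The first row exceeds 2.5% because the normal-theory limit is approximate at this sample size; it is the baseline for comparison.

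**4. Sensitivity to the discharge days, all patients read at discharge.**

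| Discharge day SCT / LCT | P(declare non-inferiority) |
|---|---|
| 7 / 10 | 85.9% |
| 10 / 14 | 70.5% |
| 14 / 17 | 47.2% |
| 7 / 7 | 84.9% |
| 10 / 10 | 68.6% |

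With the same discharge day in both arms the inflation is nearly all still there. Truncated follow-up is therefore the main driver. An earlier SCT discharge adds to it: 68.6% at 10/10 becomes 85.9% at 7/10.

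**The case against.** The strongest reply is that the time of the primary outcome is stated twice, in the abstract and in the outcome section, as day 30 after onset, and that an outcome definition governs over a sentence listing visits. The follow-up sentence can also be read benignly, with the end-of-study bracket belonging only to the 30-day alternative and the conjunction being loose drafting. Reserving the chart check for patients still in hospital makes most sense if everyone is read at a set later time. The schedule of assessments (Fig. 2) and the flowchart (Fig. 1) are not available here and may settle the timing, and the article condenses a fuller protocol.

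Much of this stands. A reader might infer that the primary outcome is in fact taken at discharge and that later relapses are lost. The documents do not support that: three places point to day 30, and a route for reaching discharged patients is planned. A reader might also take 86% as the expected error rate. It is a worst case that needs every patient in both arms to be read at discharge, against the rest of the text, together with assumed relapse of 12% v 2%; the plan itself assumes equal cure of 95%. Nor is it right to see the problem as chiefly one of SCT patients leaving first, since a common discharge day gives nearly the same result.

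The reply does not remove the contradiction. The follow-up wording offers discharge as an alternative, the contact is undated, and if a figure fixes day 30 the text still disagrees with it.

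**Conclusion.** The point holds as an inconsistency in the timing of the primary outcome, not as a demonstrated bias. The balance of the text favours day 30, but the follow-up section leaves room for a discharge reading, and wherever that is used failures after discharge can be missed. The direction is anti-conservative for non-inferiority whenever SCT has the larger excess of late failures.

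The size is unknown. Under the stated assumptions it runs from 2 percentage points of added error if a tenth of patients are read at discharge (5.6% against 3.7%) to a worst case near 86% if all are. It should be corrected because the defect concerns the primary endpoint and the remedy is almost free. Confidence is moderate, since the schedule of assessments could not be seen.

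**What to change.** Define end of study as one assessment at day 30 after onset for every patient, regardless of discharge, and remove discharge as an alternative from the follow-up section. State in the Statistical analysis section that the telephone, outpatient or chart confirmation takes place at day 30. If a discharge assessment is wanted, keep it as a separately named visit that never supplies the primary outcome. Check that the schedule of assessments says the same.

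The cost is protocol wording, plus at most one telephone call for each patient who would otherwise have been closed at discharge. Sample size, analysis method and clinical management do not change.

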### Outcome measures

The primary outcome is clinical cure at 30 days after onset (EOS). Clinical cure is defined as disappearance of all clinical symptoms which were present upon diagnosis.

The secondary outcomes are clinical improvement after 30 days, mortality at day 30 after the diagnosis, or in-hospital mortality, occurrence of adverse effects, and recurrence or complications of acute cholangitis. Clinical improvement is defined as decrease but not disappearance of clinical symptoms which were present upon diagnosis.

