### Sample size

The primary efficacy analysis will assess the non-inferiority of the clinical cure rate of SCT compared with LCT. The margin of non-inferiority is set at 10% on the statistically acceptable tolerance and clinically acceptable margin. This margin has been used as accepted in the field of infectious diseases [12, 13]. Because non-inferiority clinical trials in infectious diseases usually cannot rely on previous placebo controlled trials to calculate and estimate inferiority margins, we decided to use the rather arbitrary number of 10% as is conventionally employed. Regarding clinical cure, we judged the margin to likely be acceptable to most patients. The non-inferiority of SCT is concluded if the upper limit of the one-sided 97.5% confidence interval (CI) for the difference in clinical response (standard SCT) is less than 10%. To achieve a power of 80% with an α level of 2.5%, assuming as stated in the previous retrospective study a clinical cure rate of 95% with standard therapy with the same cure rate in SCT [6], with a non-inferiority margin of − 10%, 75 patients are required in each group.

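### Clinical cure is a day-30 snapshot of presenting symptoms, so a recurrence or complication that is re-treated and resolved by day 30 counts as a cure in the only outcome that decides non-inferiority

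*Protocol article*

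**What the plan says.** Under Outcome measures, the Protocol article states: "The primary outcome is clinical cure at 30 days after onset (EOS"), and then: "Clinical cure is defined as disappearance of all clinical symptoms which were present upon diagnosis". Clinical improvement, a secondary outcome, is built on the same presenting symptoms. The other secondary outcomes are mortality and "occurrence of adverse effects, and recurrence or complications of acute cholangitis".

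Under Assessment and follow-up, patients are assessed daily on treatment, then "at the end of therapy (EOT), and at discharge from the hospital or 30 days after onset (end of study, EOS"). Under Statistical analysis: "Clinical outcomes are confirmed by the investigators either by calling the patients by telephone or seeing them at an outpatient clinic visit", or from the chart if the patient is still in hospital.

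Under Sample size, non-inferiority is concluded from the difference in clinical response alone, with a 10-point margin, one-sided 2.5% and 75 patients per group at 95% cure in both arms. Under Statistical analysis, secondary outcomes are also to be looked at on a non-inferiority basis where appropriate; no margin is named for them.

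**The concern.** The trial asks whether antibiotics can be stopped earlier without loss of efficacy. One way in which an early stop could fail is that cholangitis returns, or a complication appears, after the last dose. Such a patient will normally be treated again, and if that succeeds before day 30 the presenting symptoms are gone. On the stated wording this patient scores the same as one who never relapsed.

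The primary comparison then measures the assigned course plus whatever rescue followed. If relapse is more frequent after the short course, successful rescue hides part of the difference. In a superiority trial that would cost power. In a non-inferiority trial it favours the positive conclusion.

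**Working it through.** **1. Does any other part of the article repair the definition?**

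- *Outcome measures* lists recurrence and complications beside clinical cure, not inside it.
- *Sample size* and *Statistical analysis* tie the decision to the cure rate only.
- *Trial interventions* says that SCT patients taken off the intervention for complications such as abscess stay in the ITT analysis and leave the per-protocol analysis. If such a patient has no presenting symptoms at day 30, ITT counts a cure and per-protocol drops the patient. Neither analysis counts a failure, and the exclusion is described only for SCT.
- *Trial oversight* lists an Event Adjudication Committee, but gives it no rule that turns recurrence into failure. The *Discussion* says that the investigators judge clinical outcomes.

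So nothing in the article changes the literal reading.

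**2. The plan's own figure.** Inputs from Sample size: p = 0.95 in both arms, margin 0.10, one-sided α 0.025, power 0.80.

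n = 2p(1−p)(z₀.₉₇₅ + z₀.₈₀)² / 0.10² = 2 × 0.95 × 0.05 × (1.960 + 0.8416)² / 0.01 = 0.095 × 7.849 / 0.01 = 74.56, rounded up to 75.

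This agrees with the plan. The issue is the outcome definition, not the arithmetic.

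**3. How much can rescue hide?** The article gives no relapse rate and no rescue rate, so all rates here are assumed. Take true failure, with relapse counted, as 5% in LCT and 15% in SCT. That deficit equals the margin, so a one-sided 2.5% test should pass about 2.5% of such trials. Let r be the share of failures re-treated and free of presenting symptoms at day 30. Two versions bracket the effect:

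- A: rescue applies to all failures in both arms, so observed failure = true failure × (1 − r).
- B: rescue applies only to the excess SCT failures, so observed SCT failure = 5% + 10% × (1 − r), and LCT stays at 5%.

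Probabilities are exact binomial enumeration at 75 per arm. Non-inferiority is declared when the upper limit of the unpooled normal interval for LCT − SCT is below 10 points.

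| r | Version | Observed cure, LCT / SCT | Observed deficit | Non-inferiority declared |
|---|---|---|---|---|
| 0% | both | 95% / 85% | 10 points | 3.7% |
| 50% | A | 97.5% / 92.5% | 5 points | 36% |
| 50% | B | 95% / 90% | 5 points | 26% |
| 80% | A | 99% / 97% | 2 points | 87% |
| 80% | B | 95% / 93% | 2 points | 58% |

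Hand check of B at 50% by normal approximation: SE = √(0.95×0.05/75 + 0.90×0.10/75) = 0.0428; (0.10 − 0.05)/0.0428 − 1.960 = −0.79; Φ(−0.79) = 21%. The same approximation gives 2.5% with no rescue and 54% for B at 80%. The pattern does not depend on the method.

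A and B have the same observed deficit at each r. The gap between them arises because A also raises the observed cure rates and so shrinks the variance. That part is not masking of the difference.

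**4. Power if the definition is tightened.** Power at 75 per arm with equal cure p is Φ(0.10/√(2p(1−p)/75) − 1.960).

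| Cure in both arms | Power at 75 per arm | n per arm for 80% |
|---|---|---|
| 95% | 80% | 75 |
| 93% | 67% | 103 |
| 90% | 53% | 142 |

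The 93% and 90% rates are assumptions.

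**The case against.** The best defence is that recurrence is not ignored. It is a pre-specified secondary outcome, so an excess after short therapy would appear in the report. A relapse still symptomatic at day 30 is already a primary failure. The article also condenses a fuller protocol, and event rules may sit there or with the adjudication committee. The first two points stand and limit the concern to events resolved by day 30. The third does not remove it: the article does not leave the definition open but states it, and the stated rule is what is at issue.

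Several stronger readings are tempting and are not supported:

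- *That the main failure of short therapy goes uncounted.* The article does not say which failure is the main one, and relapse is counted in part.
- *That deaths are scored as cures.* The article is silent on this. Mortality is collected separately, and coding death as failure is detail that a fuller document commonly holds.
- *That 87% is the size of the problem.* It needs rescue in both arms and an observed LCT cure of 99%, against the 95% planned.
- *That a stricter endpoint needs no new data.* Antibiotics after the assigned course are not a listed outcome, and chart review is described only for patients still in hospital.
- *That power will fall.* The article does not show whether the cited 95% already counts relapse as failure.

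**Conclusion.** The concern holds in limited form. As defined, a recurrence or complication that is re-treated and free of presenting symptoms by day 30 is a cure in the outcome that alone decides non-inferiority. The secondary outcome "recurrence or complications of acute cholangitis" makes such events visible but does not protect the conclusion.

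The bias runs towards no difference whenever relapse is more frequent in SCT and some of it is rescued. If relapse is equally frequent and equally rescued in both arms, the comparison is not shifted. In the illustration, a deficit as large as the margin passes in about 4% of trials without rescue, 26-36% with half rescued and 58-87% with 80% rescued. These figures show what the rule permits; they do not predict this trial. Because the rule decides who counts as a failure in the deciding test, the wording should be amended.

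**What to change.** Define clinical cure as: alive at day 30, all presenting symptoms gone, and no recurrence or infectious complication of cholangitis by day 30.

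- **Window.** Count events in both arms over the same window from a common origin, either onset or randomisation. Do not count from the end of assigned therapy. If therapy began at onset, a 5-day course would leave 30 − 5 = 25 days at risk and a 7-day course 30 − 7 = 23, fewer still for longer LCT courses. That would count against SCT.
- **Events.** Use the recurrence and complication events already listed as secondary outcomes, judged by criteria applied identically in both arms. Antibiotics given as part of the assigned course are not an event.
- **Optional component.** If restarting antibiotics after the assigned course is added, record it at the day-30 contact. State that it is a clinician's decision in an open-label trial and could itself differ by arm.
- **Continuity.** Keep the current definition as a secondary outcome.

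The cost is an amendment of the primary endpoint wording, and possibly one added question at the day-30 contact. The cure rate may be below 95%, so restate the power under the new definition (67% at 93% and 53% at 90% with 75 per arm). Also state whether the 95% from the retrospective study treated relapse as failure.

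### The secondary outcome of clinical improvement counts cured patients as not improved, so it has no favourable direction and can rank the arms the wrong way round.

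*Protocol article*

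**What the plan says.** The Outcome measures section of the Protocol article defines two outcomes on the same set of symptoms. For the primary outcome: "Clinical cure is defined as disappearance of all clinical symptoms which were present upon diagnosis". For the secondary outcome: "Clinical improvement is defined as decrease but not disappearance of clinical symptoms which were present upon diagnosis". Improvement heads the list of secondary outcomes: "The secondary outcomes are clinical improvement after 30 days, mortality at day 30 after the diagnosis".

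The Statistical analysis section then states: "Secondary outcomes will also be analysed under a non-inferiority assumption, as appropriate". The same section makes all P values one-sided at 0.025.

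The only margin in the article is in the Sample size section: "The margin of non-inferiority is set at 10% on the statistically acceptable tolerance and clinically acceptable margin". That section ties the margin to the clinical cure rate. No margin is given for improvement. Nothing in the article combines improvement with cure, restricts it to uncured patients, exempts it from non-inferiority analysis or states which direction is favourable.

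**The concern.** The two definitions are mutually exclusive. A patient can be absent from the improved category for opposite reasons: all symptoms have gone (the best result), or symptoms have not decreased or the patient has died (the worst). A non-inferiority analysis needs an outcome for which more is better or more is worse, and this one is neither.

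At stake is how the first-listed secondary outcome will be read. A higher improvement rate on SCT could be presented as supporting the shorter course when it reflects fewer cures. A lower rate could count against SCT when it reflects more cures.

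**Working it through.** **Inputs from the Protocol article.** 75 patients per arm; 95% cure assumed in both arms; margin 10 points, set for cure; one-sided α 2.5%; power 80% (all Sample size); normal-theory test for binomial proportions, specified for the primary outcome (Statistical analysis).

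**Step 1: reproduce the plan's own figure.** n per arm = (1.960 + 0.842)² × 2 × 0.95 × 0.05 / 0.10² = 74.6, rounded up to 75. This agrees with the article.

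**Step 2: what the definition implies under the plan's assumption.** If 95% of LCT patients are cured, at most 5% can be improved. SCT's true improvement rate then cannot be 10 points lower than LCT's. If the cure margin were carried over, the null hypothesis of inferiority on improvement could not be true.

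**Step 3: two illustrative results.** The counts are assumptions chosen to show the direction. Differences are LCT minus SCT, with upper limit = (p_L − p_S) + 1.96 × √[p_L(1−p_L)/75 + p_S(1−p_S)/75].

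| Case | Outcome | LCT | SCT | Difference | 1.96 × SE | Upper limit |
|---|---|---|---|---|---|---|
| SCT cures fewer | Cure | 72/75 | 63/75 | +12.0 | 9.4 | 21.4% |
| | Improvement as defined | 2/75 | 10/75 | −10.7 | 8.5 | −2.2% |
| | Cured or improved | 74/75 | 73/75 | +1.3 | 4.5 | 5.8% |
| SCT cures more | Cure | 66/75 | 72/75 | −8.0 | 8.6 | 0.6% |
| | Improvement as defined | 8/75 | 2/75 | +8.0 | 7.9 | 15.9% |
| | Cured or improved | 74/75 | 74/75 | 0.0 | 3.7 | 3.7% |

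In the first case SCT fails clearly on cure, yet on improvement the whole interval lies on its side of zero. In the second case SCT does better on cure, yet would fail on improvement at a borrowed 10% margin.

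**Step 4: how often this would happen.** Exact binomial enumeration with 75 per arm, the same limit and the cure margin borrowed for every outcome. Improvement rates are assumptions.

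| LCT cured/improved | SCT cured/improved | Non-inferior on cure | Non-inferior on improvement | Non-inferior on cured or improved |
|---|---|---|---|---|
| 95% / 4% | 85% / 14% | 4% | 99.5% | 99.6% |
| 95% / 4% | 80% / 19% | 0.3% | 99.9% | 99.6% |
| 95% / 4% | 80% / 4% | 0.3% | 88% | 0.3% |
| 80% / 19% | 95% / 4% | 99.9% | 0.3% | 99.6% |

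In the first two rows, SCT's improvement rate would also be significantly higher than LCT's in 61% and 86% of trials. In the third row the lost cures become non-responders. Improvement then does not rise, but it hides the loss in 88% of trials, whereas cured-or-improved hides it in 0.3%.

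**The case against.** The strongest reply is that the non-inferiority sentence ends with a qualifier leaving the authors to decide where it is appropriate, so they are not committed to testing improvement this way. That is true, and an unshown analysis plan may say more. It does not repair the definition, which is fixed in the article and misorders the arms under any comparison that treats improvement as favourable.

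Second, the outcome is secondary, and cure will be reported beside it. In the first illustration SCT fails the primary outcome by a wide margin (upper limit 21.4%), so improvement alone would not carry the trial. This stands and limits the importance of the point.

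Third, the inversion needs lost cures to become partial improvements, and at the planned 95% cure rate fewer than four patients per arm (5% of 75 = 3.75) are expected to be uncured. The illustrations depart from that rate in one arm each. This also stands: the outcome can mislead, but need not.

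A reader might go further and infer that deaths will be judged against a 10% margin, or that a benefit in adverse effects could never be shown. The article supports neither. It sets 10% for clinical cure only; secondary margins are unstated, which an article may leave to fuller documents. An example of 4/75 SCT against 1/75 LCT deaths would pass at 10% by the Wald limit (9.7%) but fail by Newcombe's (11.7%), and the article fixes neither margin nor method for deaths. A one-sided limit below zero would show a reduction in adverse effects; testing them two-sided is a preference.

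**Conclusion.** The point holds for clinical improvement. As defined, the outcome excludes cured patients and has no favourable direction, and the article neither exempts it from non-inferiority analysis nor says how it is to be read. It can favour an arm that is 12 points worse on cure (upper limit −2.2%) and count against one that is 8 points better (upper limit 15.9%, a failure only if the cure margin is borrowed). These figures rest on assumed counts, a Wald limit, and lost cures becoming partial improvements. The defect itself follows from the wording alone.

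The primary analysis and the sample size of 75 per arm are unaffected. This is a correction to a secondary outcome that should be made. It is not a finding about mortality or adverse effects.

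**What to change.** In Outcome measures, redefine the secondary outcome as decrease or disappearance of the presenting symptoms, that is, cured or improved. More is then better.

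Also report the mutually exclusive categories (cured, improved, not improved or died) descriptively by arm. This table is needed because cured-or-improved is blind by design to movement between cure and partial improvement: in the first illustration it gives 74/75 against 73/75, which removes the false advantage for SCT but does not show the loss of cures.

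The cost is about two sentences in the protocol or analysis plan, settled before results by arm are seen. The symptom assessment already planned supplies everything required, so no new data are needed.

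### Clinical improvement is defined so that cured patients count as not improved, leaving this secondary outcome without a valid favourable direction for a non-inferiority test

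*Protocol article*

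**What the plan says.** The Outcome measures section of the protocol article sets the primary outcome, assessed 30 days after onset: "Clinical cure is defined as disappearance of all clinical symptoms which were present upon diagnosis". The list of secondary outcomes opens with improvement: "The secondary outcomes are clinical improvement after 30 days, mortality at day 30 after the diagnosis". In-hospital mortality, adverse effects, and recurrence or complications follow. Improvement is then defined: "Clinical improvement is defined as decrease but not disappearance of clinical symptoms which were present upon diagnosis".

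The Statistical analysis section says: "Secondary outcomes will also be analysed under a non-inferiority assumption, as appropriate". It adds: "All *P* values are one-sided, and *P* < 0.025 is considered statistically significant".

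The Sample size section assumes "a clinical cure rate of 95% with standard therapy with the same cure rate in SCT", with a 10-point margin and 75 patients per arm. The margin is argued for clinical cure.

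The article does not say that cured patients also count as improved. It does not say whether a high or a low proportion improved is favourable, and it does not exempt improvement from the non-inferiority analysis.

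**The concern.** Under the two definitions each patient falls into one of three classes: cured, improved but not cured, or neither (including death). Clinical improvement is the middle class taken alone. Its complement pools the best result with the worst.

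A rise in this proportion can mean that failures became improvements, which is good, or that cures became improvements, which is bad. The proportion does not show which. A non-inferiority test needs a favourable direction, and this outcome has none that is valid.

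Improvement is the only other listed outcome on the same symptom-response scale as cure, so readers will look to it for support of the primary result. Tested with higher as better, it could reassure them about the short course when the short course cures fewer patients.

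**Working it through.** **Inputs from the protocol.** Cure 95% in both arms, margin 10 points, one-sided alpha 0.025, power 80%, 75 per arm.

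**Assumptions added here.** (a) f is the share of non-cured patients who are improved. The protocol does not give it, so it is varied from 0.2 to 1.0 and is equal in both arms unless stated. (b) The 10-point cure margin is applied to improvement. (c) Non-inferiority is declared when the lower unpooled normal 95% limit for SCT minus LCT lies above −10 points. Probabilities come from exact binomial enumeration with 75 per arm.

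**1. The plan's own figure.** n per arm = 2 × 0.95 × 0.05 × (1.95996 + 0.84162)² / 0.10² = 74.56, rounded up to 75. Power at 75 by the same approximation is 80.2%. The stated sample size reproduces.

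**2. Improvement in terms of cure.** Improvement rate = (1 − cure rate) × f.

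**3. Ceiling in the control arm.** At 95% cure, LCT improvement = 0.05 × f, at most 5%. SCT improvement cannot be below 0, so the largest possible true deficit is 5 points, half of the 10-point margin.

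**4. Chance of declaring non-inferiority when LCT cures 95%.**

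| f | SCT cure | Improved, LCT v SCT | Passes on improvement | Passes on cure |
|---|---|---|---|---|
| 0.6 | 95% | 3% v 3% | 0.934 | 0.817 |
| 0.6 | 90% | 3% v 6% | 0.975 | 0.259 |
| 0.6 | 85% | 3% v 9% | 0.991 | 0.037 |
| 0.6 | 80% | 3% v 12% | 0.997 | 0.003 |
| 1.0 | 95% | 5% v 5% | 0.817 | 0.817 |
| 1.0 | 90% | 5% v 10% | 0.948 | 0.259 |
| 1.0 | 85% | 5% v 15% | 0.990 | 0.037 |
| 1.0 | 80% | 5% v 20% | 0.999 | 0.003 |

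As SCT cures fewer patients, its chance of passing on improvement rises. With SCT cure at 80%, that chance is 0.997 to 0.999 over f = 0.2 to 1.0.

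**5. When the ordering reverses.** SCT scores lower on improvement only if (1 − SCT cure) × f(SCT) < 0.05 × f(LCT), that is, if f(SCT)/f(LCT) < 0.05 / (1 − SCT cure). The break-even ratio is 0.05/0.10 = 1/2 at SCT cure 90%, 0.05/0.15 = 1/3 at 85% and 0.05/0.20 = 1/4 at 80%. Below these, the lost cures are mostly failures or deaths.

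**6. Reading lower as better does not repair it.** With LCT cure 95%, SCT cure 80% and f = 0.2, improvement is 1% v 4%. A lower-is-better test with the same margin passes in 0.742 of trials, while cure passes in 0.003. Failures and deaths count as not improved, so they help the arm that has them.

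**7. The cumulative outcome.** With cure 95% v 80% and f = 0.6, cure or improvement is 0.95 + 0.03 = 98% v 0.80 + 0.12 = 92%. It passes in 0.279 of trials, against 0.997 for the present definition.

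**The case against.** The strongest reply has four parts.

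First, the non-inferiority sentence is qualified. It applies where suitable, the list mixes favourable and unfavourable outcomes, and direction and margin for each may sit in an analysis plan that is not shown. This stands in part. A reader might infer that the protocol commits itself to a higher-is-better test of improvement; it does not. But the definition is fixed in the protocol, and an analysis plan that keeps it cannot give the proportion a sound direction.

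Second, a reader might infer that fewer cures means more improvements by definition, so that this outcome must contradict the primary. That is too strong. It holds when non-cured patients improve at similar rates in the two arms and reverses below the break-even ratios in the working. At the planned 95% cure in both arms, improvement and cure would both usually pass (0.934 and 0.817 at f = 0.6).

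Third, a reader might infer that a worse short course would be declared better on improvement. At 5% v 15% improved, a superiority test at one-sided 0.025 would succeed in 0.556 of trials, but the protocol plans no such test for this outcome. Likewise, the mirror case, where SCT cures more yet fails on improvement (0.037 at cure 95% SCT v 85% LCT, f = 1), needs a control cure rate well below the planned 95%.

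Fourth, if cure and improvement are both reported, a reader can add them, and being listed first confers no stated priority. This is correct and limits the harm. It does not make a separate test of the middle class interpretable.

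**Conclusion.** The point holds as a defect of definition. Taken alone, improvement groups cured patients with failures and deaths, so neither a high nor a low proportion is reliably good. If it is tested for non-inferiority with higher as better, the arm with fewer cures will tend to look better unless its lost cures are mostly failures or deaths.

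The size depends on two assumptions that the protocol does not state: the share of non-cured patients who improve, and use of the cure margin for this outcome. With every non-cured patient improved and cure of 95% v 85%, SCT passes on improvement in about 99% of trials and on cure in about 4%. The ceiling needs neither the share nor a test: at the assumed 95% cure, the true deficit on improvement cannot exceed 5 points.

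The primary outcome, the sample size and the primary conclusion are not affected.

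**What to change.** Redefine the secondary outcome cumulatively as cure or improvement at day 30, meaning that presenting symptoms have decreased or gone, so that higher is better. Alternatively, compare the three ordered categories (cured / improved / not improved or dead) in one ordinal analysis. In either case, do not test improved-but-not-cured on its own; it can still be shown as one row of the outcome table.

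If the cumulative outcome is tested for non-inferiority, state its direction and margin in the analysis plan, since the 10-point margin is argued only for cure.

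The cost is one sentence in the outcome definition, with a matching line in the analysis plan. No new data are needed, because the same symptom assessment supplies all three classes.
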